#### Dialysis at Home

Participants will be randomized individually using minimization and two stratification factors: the language spoken at home and the research site. An interactive voice response system will be used for randomization; this allows for research staff to call a third party—the National Health Medical Research Council Clinical Trials Centre—which allocates the randomization order.

### Timeline

The study timeline will include four data collection timepoints: baseline and 3-month, 6-month, and 12-month follow-ups (Figure 1).

**Figure 1 figure1:**
[figure not shown]
Study flow and timeline. SUCCESS: Supporting Culturally and Linguistically Diverse CKD Patients to Engage in Shared Decision-Making Successfully.

### Study Outcomes

Once informed consent is obtained, baseline measures will be collected, including demographics, dialysis history, cognition level, and health and digital literacy status (Table 1 [20-30]). Our primary outcomes are health literacy, shared decision-making, and rates of unscheduled health encounters; these will be assessed at 3, 6, and 12 months of app usage (Table 1). Secondary outcomes include patient-reported outcomes and clinical outcomes; these will also be assessed at 3, 6, and 12 months of app usage (Table 1).

**Table 1 table1:** Measurements collected throughout the trial.

Measure and description			Timepoint (month)							
			0		3		6		12	
**Baseline measurements**										
	Demographics: age, gender, country of birth, language spoken at home, Aboriginal and Torres Strait Islander status, and highest education attained.	✓^a^								
	Dialysis history: mode of dialysis (hemodialysis or peritoneal dialysis), location of treatment (home or in-center), dialysis schedule (frequency of dialysis per week), and dialysis vintage (years on dialysis).	✓								
	Cognition impairment: the MoCA^b^ is a screening tool developed to assist clinicians in the detection of cognitive impairment [20]. It measures a person’s orientation in time and space, short-term memory, abstract reasoning, attention, and many other aspects of cognitive ability. The MoCA tool was chosen as it is a more sensitive tool for detecting mild cognitive impairment compared to the MMSE^c^ [21]. The MoCA returns a cognitive ability score ranging from 0 to 30, where a score of ≤26 suggests cognitive impairment [20].	✓								
	Health literacy, self-report: the brief health literacy screener is a single-item screener to identify people with inadequate levels of functional health literacy in clinical settings [22,23]. The item asks, “How confident are you filling out medical forms by yourself?”; the item is rated on a 5-point response scale ranging from “not at all” to “extremely.” The threshold for inadequate health literacy is “somewhat” or less.	✓								
	Health literacy, performance-based: a brief comprehension test based on instructions similar to those found on a packet of aspirin bought over the counter [24]. Participants are asked to read a fictitious medicine label and respond to four questions, such as “What is the maximum number of days you may take this medicine?” and “List one condition for which you might take the tablet.” The task was developed according to a conceptual framework that defines literacy as an ability to fulfill goal-directed tasks, in this case, in a health context. Health literacy is categorized as high (maximum score), medium (one error), or low (more than one error).	✓								
	Digital literacy: the assessment of digital literacy was adapted from a validated instrument, the MACL^d^, a 7-point Likert scale consisting of statements about attitudes toward computers [25]. For the purpose of this study, the questions were modified to reflect the context of smartphone usage, such as “I can switch on and off a mobile phone.” Participants’ mobile phone locus of control was assessed to understand how well they believe that they have control over the outcomes of events of their smartphone usage [25].	✓								
**Primary outcomes: patient-reported outcomes**										
	Health literacy skills: the HLQ^e^, a multidimensional tool that measures health literacy across nine distinct conceptual domains, will be used. The median reliability of the HLQ domains is 0.88, with a range from 0.77 to 0.90 [26]. For the purpose of this study, we have selected three to domains to explore: Domain 2: have sufficient information to manage my health Domain 6: ability to actively engage with health care providers Domain 9: understand health information well enough to know what to do. Domain 2 assesses the strength of a participant’s agreement with the statement on a 4-point ordinal scale, ranging from 1 (“strongly disagree”) to 4 (“strongly agree”); domains 6 and 9 assess a participant’s perceived ease in task completion on a 5-point ordinal scale, ranging from 1 (“always difficult”) to 5 (“very easy”).	✓		✓		✓				✓
	Decision self-efficacy: the Decision Self-Efficacy Scale [23] measures self-confidence or belief in one’s ability to make decisions, including participation in shared decision-making. This item consists of 11 questions where participants rate their confidence engaging in decision-making behaviors, such as “Getting the facts about the medication choices available.” Items are rated on a 5-point ordinal scale ranging from 1 (“not at all confident”) to 5 (“very confident”).	✓		✓		✓				✓
	Rates of unscheduled health encounters: this includes unexpected hospital and emergency visits and unscheduled dialysis events in the past 3 months as reported by participants; this is also verified by extracting this information from electronic medical records.			✓		✓				✓

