#### Dialysis at In-Center Units

It is standard practice for patients on hemodialysis at the in-center units to receive dialysis treatment three times a week. Patients receiving in-center dialysis always attend on the same days: either Mondays, Wednesdays, and Fridays or Tuesdays, Thursdays, and Saturdays. Therefore, a pragmatic approach will be used at each center by randomizing patients according to their pattern of attendance. Depending on the center, all participants attending Monday, Wednesday, and Friday will be assigned to the same study intervention group, and those attending Tuesday, Thursday, and Saturday will be assigned to the alternate study intervention group.

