**Secondary outcomes: clinical outcomes**										
	Changes in symptom burden: the POS^h^ is a widely used and validated instrument used in clinical care and research. The POS-Renal is a short measure (11 questions) that collects information on the most common symptoms that renal patients experience [29].	✓		✓		✓				✓
	Nutritional status: the PG-SGA^i^ is a standard nutritional assessment tool measuring clinical indices (ie, weight, intake, symptoms, functional status, disease state, metabolic stress, and nutritional physical examination) in a range of chronic conditions [30]. The PG-SGA enables the patient and professional to quickly and easily assess and monitor the risk for malnutrition and to evaluate effects of interventions.	✓		✓		✓				✓
	Interdialytic weight gain: this is a measure of weight gained between two consecutive dialysis sessions. The measure gives an indication of whether patients are adhering to fluid restrictions and is recorded at each dialysis session; the monthly average is easily calculated for each patient.	✓		✓		✓				✓
	Key performance indicators: typical key performance indicators for dialysis will be linked and extracted from the Australian and New Zealand Dialysis and Transplant registry. This will include demographics, ethnicity, anthropometry, comorbidities, course of treatment, and survival rates.	✓		✓		✓				✓
	App analytics—the following information will be extracted using Google Analytics: How many people have registered or logged in? How often do people log in? At what times? How does this relate to their dialysis times? How long do people stay logged in? Time between visits Number of times people access app features (eg, quizzes and videos) Number of visits to each page and subpage.	✓		✓		✓				✓

^a^A checkmark indicates that the measure will be performed at the indicated timepoint.

^b^MoCA: Montreal Cognitive Assessment.

^c^MMSE: Mini–Mental State Examination.

^d^MACL: Multicomponent Assessment of Computer Literacy.

^e^HLQ: Health Literacy Questionnaire.

^f^EQ-5D-5L: 5-level EQ-5D.

^g^SUCCESS: Supporting Culturally and Linguistically Diverse CKD Patients to Engage in Shared Decision-Making Successfully.

^h^POS: Palliative care Outcome Scale.

^i^PG-SGA: Patient-Generated Subjective Global Assessment.

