#### Missing Data

We will use best practice to decide when imputation is necessary for missing data, except for the outcome data, considering the percentage of missing data and plausibility of the “missing at random” assumption [32]. Where there is a large proportion of missing data, we will consider using a complete case or pairwise deletion approach. We will also perform sensitivity analyses to evaluate the robustness of our results. For outcome data, we will not use imputation methods and will only exclude participants who do not have baseline data and at least one follow-up outcome measure.

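### Unscheduled health encounters, a primary outcome, is the only outcome row in Table 1 without a month-0 measurement, so prior use can be neither balance-checked nor adjusted for as the schedule stands

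*Protocol article*

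**What the plan says.** Table 1 gives the encounter outcome as "unexpected hospital and emergency visits and unscheduled dialysis events in the past 3 months as reported by participants", and adds that "this is also verified by extracting this information from electronic medical records". Its row carries three ticks, at months 3, 6 and 12; the month-0 cell is empty. The table footnote fixes what a tick means: "A checkmark indicates that the measure will be performed at the indicated timepoint".

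The other two primary outcomes, the Health Literacy Questionnaire (HLQ) and the Decision Self-Efficacy Scale, are ticked at months 0, 3, 6 and 12. So is every secondary row, including app analytics. The Timeline section makes baseline one of the collection points: "The study timeline will include four data collection timepoints: baseline and 3-month, 6-month, and 12-month follow-ups". The baseline measures named in the Study Outcomes text do not include encounters.

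Three further statements bear on the point:

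- **Dialysis at In-Center Units.** Depending on the center, "all participants attending Monday, Wednesday, and Friday will be assigned to the same study intervention group", and the other day pattern goes to the other arm.
- **Data Analysis, Overview.** The models contain study arm, a random effect for center, and a covariate for home versus in-center care. No baseline value of the outcome is named for any outcome.
- **Missing Data.** For outcome data the analysis "will only exclude participants who do not have baseline data and at least one follow-up outcome measure".

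**The concern.** Earlier unscheduled use of care can be expected to predict later unscheduled use, so a pre-enrolment count is the natural covariate for this outcome and the most direct check that the arms started alike. The schedule does not collect one. An analysis plan written later cannot adjust for a value that was never obtained, so this is a matter of the data-collection schedule and not a detail that can wait for the SAP.

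The allocation method raises the stakes. Home patients are randomized individually. In-center patients follow their attendance days, so within a center one whole day-pattern group forms the intervention arm and the other forms the control arm. With few such groups, a chance difference in prior use between them is less reliably averaged out than under individual randomization, and it would feed into the estimated effect of the app on a primary endpoint.

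**Working it through.** **1. The schedule.** Ticks by outcome row in Table 1:

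| Row | 0 | 3 | 6 | 12 |
|---|---|---|---|---|
| HLQ domains | yes | yes | yes | yes |
| Decision self-efficacy | yes | yes | yes | yes |
| Unscheduled encounters | no | yes | yes | yes |
| All secondary rows | yes | yes | yes | yes |

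The exception is confined to one row. No practical reason for it is apparent: the item looks back three months, baseline data are collected in person, and electronic records are already a source.

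**2. What the model terms can absorb.** Study Setting lists six teaching hospitals and six community centers. If each ran one in-center unit with both day patterns, there would be at most 12 × 2 = 24 day groups. Within one center the contrast between day groups is the contrast between arms. A center effect removes differences between centers, and the home/in-center covariate removes differences between those two types of patient. Neither term can separate a day-group difference in prior use from the arm effect.

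**3. The plan's own figure.** The only power statement concerns the HLQ: 384 participants, 20% loss, a difference of 0.25, two-sided 5%. Evaluable: 384 × 0.8 = 307.2, or 153.6 per arm. Power = Φ(0.25 / (SD × √(2/153.6)) − 1.96).

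- SD 0.60: Φ(3.65 − 1.96) = 95.5%; the plan says above 90%.
- SD 0.75: Φ(2.92 − 1.96) = 83.2%; the plan says at least 80%.

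Both reproduce, and neither depends on the encounter row. The document gives no encounter rate, variance or correlation.

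**4. Size of the precision loss, on an assumption.** Let r be the correlation between a participant's counts before and after enrolment. In a linear model, adjustment removes a share r² of the residual variance, and n participants then carry the information of n / (1 − r²).

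- r = 0.3: r² = 9%; 307.2 / 0.91 ≈ 338.
- r = 0.5: r² = 25%; 307.2 / 0.75 ≈ 410.

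**5. Size of the imbalance effect, on the same assumption.** If the arms differ in prior use by d standard deviations, and counts before and after have equal variance, about r × d carries into the unadjusted follow-up difference: 0.3d to 0.5d. The documents give no value for d.

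**6. The inclusion rule.** In the Missing Data sentence the word outcome is attached to the follow-up measure and not to the baseline data. Study Outcomes uses the term baseline measures for participant characteristics, dialysis history, cognition, and health and digital literacy, which everyone is scheduled to have. Read that way, the rule works for encounters. The sentence does not settle the reading itself.

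**The case against.** The strongest reply is that randomized arms can be compared on follow-up event rates without any baseline value. That is correct. The stated models name no baseline term even for the outcomes that have one, so a month-0 tick alone would not change the stated analysis, and the choice of covariates may belong to an SAP that is not shown. This stands, and it is why the fix must include the covariate as well as the tick.

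It can also be said that imbalance from allocating whole day groups affects every outcome, and that both day patterns are compared inside each center. Both are true. But the other outcomes have a month-0 value that could be used, and the within-center contrast is exactly where day group and arm coincide. Nothing in the document shows that prior use does differ by attendance day; the risk is possible, not demonstrated.

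The r² figures measure an individual-level precision gain under a linear model. They do not measure imbalance between day groups, and a count outcome would not follow them exactly.

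A reader might infer two stronger things. One is that the Missing Data rule leaves none of the 384 participants eligible for the encounter analysis. This requires adding the words of the same outcome to a sentence that does not contain them, and the Study Outcomes text points the other way. The other is that prior use is lost for good. Only the self-reported count is lost for participants already past baseline. The records that already serve this outcome could probably supply a pre-enrolment count; the plan simply does not schedule it.

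**Conclusion.** The point holds as a correctable design weakness on a primary outcome. Encounters is the only outcome row without a month-0 measurement, so as scheduled there is no pre-enrolment count for a balance check or for adjustment. The between-arm comparison remains valid. What is lost is precision and the means to correct a difference in prior use between in-center day groups.

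With an assumed correlation of 0.3 to 0.5 and a linear approximation, the forgone reduction in residual variance is about 9% to 25%. The correlation is not in the document, and the gain shrinks toward nothing if it is low. No stated sample-size figure changes. The inclusion rule is unclear in wording, but the documents do not support reading it as impossible to meet.

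**What to change.** 1. Add a month-0 tick to the encounter row of Table 1 and put the same three-month look-back question at the existing baseline visit.
2. Extend the planned record extraction to the three months before enrolment. Recruitment has begun, so use the records to fill month 0 for participants already enrolled, and note which source each baseline count came from.
3. Name this count as a covariate in the encounter model and report it by arm, and by day group for in-center patients.
4. In Missing Data, state that baseline data means the general baseline measures, so that the rule is not taken to require a baseline value of each outcome.

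The cost is one more question, a longer look-back in an extraction already planned, and one clarified sentence. No new visit is needed. If the sponsor prefers not to collect the count, the protocol should at least say that encounters are analyzed without a baseline value, and still make the fourth change.

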**Methods:**

We designed a multicenter pragmatic randomized controlled trial to compare the SUCCESS app plus usual care (intervention) to usual care alone (control). A total of 384 participants receiving in-center or home-based hemodialysis or peritoneal dialysis will be recruited from six local health districts in the Greater Sydney region, New South Wales, Australia. To avoid intervention contamination, a pragmatic randomization approach will be used for participants undergoing in-center dialysis, in which randomization will be based on the days they receive hemodialysis and by center (ie, Monday, Wednesday, and Friday or Tuesday, Thursday, and Saturday). Participants undergoing home-based dialysis will be individually randomized centrally using simple randomization and two stratification factors: language spoken at home and research site. Consenting participants will be invited to use the SUCCESS app for 12 months. The primary endpoints, which will be assessed after 3, 6, and 12 months of app usage, are health literacy skills, evaluated using the Health Literacy Questionnaire; decision self-efficacy, evaluated using the Decision Self-Efficacy Scale; and rates of unscheduled health encounters. Secondary outcomes include patient-reported outcomes (ie, quality of life, evaluated with the 5-level EQ-5D; knowledge; confidence; health behavior; and self-management) and clinical outcomes (ie, symptom burden, evaluated with the Palliative care Outcome Scale–Renal; nutritional status, evaluated with the Patient-Generated Subjective Global Assessment; and intradialytic weight gain). App engagement will be determined via app analytics. All analyses will be undertaken using an intention-to-treat approach comparing the intervention and usual care arms.

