### Data Analysis

#### Overview

Analysis of data will occur using an intention-to-treat approach and will compare the intervention and usual care arms. For continuous and binary outcomes, linear and logistic regression models will be used, respectively, with study arm as a covariate. All models will also be adjusted for center using a random effect, and the type of patient (ie, receiving home-based or in-center care) will be adjusted for using a covariate.

Qualitative data will be analyzed using the Framework approach to thematic analysis [31]. Framework analysis is a matrix-based approach with columns depicting themes and rows listing the cases, enabling the relationship between themes and cases to be explored. The first step involves familiarization with the data, where one or two researchers will review the transcript and, using an inductive approach, they will then develop a list of emerging topics and salient themes. These initial impressions will form the basis of the coding framework. Then, additional researchers will independently read a subset of transcripts and review the framework, which will further be revised with continuous discussion if needed. One researcher will then code all the interviews into the final framework, of which a random subset (10%) will be double coded by an additional researcher to ensure rigor. Similarities or differences will be discussed and reassessed. Microsoft Excel will be used to summarize the themes and supporting quotes from each transcript in the framework. Prominent themes arising from the framework will be identified and discussed in-depth with the research team.

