### Sample Size

Our sample size has been calculated based on the primary outcome of the three Health Literacy Questionnaire (HLQ) domains. We assumed a minimal clinically important difference of 0.25 units in any one of the three HLQ domains. A sample size of 384 participants would result in greater than 90% power to detect a 0.25-unit change in an HLQ domain between the two arms, assuming an SD of 0.60, and at least 80% power, assuming an SD of 0.75. These SD values are based on published literature and equate to a standardized difference of 0.42 and 0.33, respectively; a standardized difference of 0.5 is considered a medium effect [33,34]. Our power calculation is based on conducting our analyses using 2-sided tests, a 5% significance level, and assuming 20% loss to follow-up (eg, due to death or kidney transplant).

For qualitative interviews, a maximum total sample size of 40 participants is planned. Interviews will continue until data saturation or until the maximum total sample size is reached.

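### The primary encounter rate is collected by 3-month recall at months 3, 6 and 12, which leaves out months 7-9 and events after the last completed visit, and no named model fits a rate with unequal observation time

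*Protocol article*

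**What the plan says.** The Abstract lists "rates of unscheduled health encounters" among the primary endpoints, beside the Health Literacy Questionnaire (HLQ) and decision self-efficacy.

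- **Measurement.** Table 1 counts unexpected hospital and emergency visits and "unscheduled dialysis events in the past 3 months as reported by participants". On records it adds that "this is also verified by extracting this information from electronic medical records".
- **Timing.** Study Outcomes says of the primary outcomes that "these will be assessed at 3, 6, and 12 months of app usage". The Timeline section gives "four data collection timepoints: baseline and 3-month, 6-month, and 12-month follow-ups". There is no 9-month visit, and Table 1 has no month-0 tick for encounters.
- **Analysis.** Data Analysis, Overview: "For continuous and binary outcomes, linear and logistic regression models will be used". All models carry a random effect for center and a covariate for home or in-center care. No count or rate model and no exposure term is named.
- **Attrition.** The Sample Size section works from the HLQ domains only, "assuming 20% loss to follow-up (eg, due to death or kidney transplant". Missing Data says that outcomes will not be imputed.

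**The concern.** A rate needs a numerator and an observation time that match. Here the numerator comes from three separate recall windows, and the last two do not adjoin. A participant who dies or is transplanted between visits makes no report for the final stretch of follow-up, when unscheduled encounters may be frequent. Records could fill both gaps, but the article gives them only a verifying role for the recalled information.

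The model named later matters less than the collection. An analysis plan can add a count model, but it cannot recover events that nobody collected. At stake are some power on a primary outcome and, if early exit differs between arms, a biased comparison wherever counts are not related to time observed.

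**Working it through.** **1. The plan's own figure.** The only power statement is for the HLQ: 384 participants, 20% loss, difference 0.25, two-sided 5%. Analyzed per arm: 384 × 0.8 / 2 = 153.6. Power = Φ(0.25 / (SD × √(2/153.6)) − 1.96).
- SD 0.60: Φ(3.651 − 1.96) = 95.5% (stated: above 90%).
- SD 0.75: Φ(2.921 − 1.96) = 83.2% (stated: at least 80%).

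Both reproduce and are unaffected by this point. No event rate, dispersion or rate ratio is given for encounters.

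**2. Coverage of the recall windows.**

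| Visit | Months covered |
|---|---|
| 3 | 0 to 3 |
| 6 | 3 to 6 |
| 12 | 9 to 12 |

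Total 3 + 3 + 3 = 9 of 12 months (75%). The uncovered stretch, from the end of month 6 to the end of month 9, is 25% of the year.

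**3. Cost of the gap, under assumptions.** Assumed: 192 per arm, rate ratio 0.70, 20% leaving at a uniform time in the year, no clustering, gamma-Poisson counts with dispersion k. Two separate simulations of 600 trials per setting gave these powers for a negative binomial (NB) model with person-time:

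| Control rate per year, k | NB, 12 months | NB, 9 months | Loss (points) |
|---|---|---|---|
| 1.5, k = 1 | 65.3% / 73% | 58.8% / 63% | 6.5 / 10 |
| 2.5, k = 0.5 | 95.0% / 91% | 89.8% / 87% | 5.2 / 4 |
| 1.0, k = 2 | 46.5% / 48% | 42.7% / 41% | 3.8 / 7 |

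The two runs differ by up to 8 points in level, so a closed-form check is useful. Each participant contributes information μ/(1 + kμ), where μ is the expected count. The variance of the log rate ratio is 1/(192 × I_control) + 1/(192 × I_app), where I is the mean information per participant. For rate 1.5 and k = 1, the app-arm rate is 1.5 × 0.70 = 1.05.
- **12 months.** Completers contribute 1.5/2.5 = 0.600 and 1.05/2.05 = 0.512. Early leavers average 1 − ln(2.5)/1.5 = 0.389 and 1 − ln(2.05)/1.05 = 0.316. Weighted 0.8 and 0.2: 0.558 and 0.473. The standard error is 0.1426, z = 0.3567/0.1426 = 2.50, and power is Φ(0.54) = 70.6%.
- **9 months, completed windows only.** Completers contribute 1.125/2.125 = 0.529 and 0.7875/1.7875 = 0.441. Of early leavers, a quarter give nothing, a quarter give one window and half give two, averaging 0.283 and 0.224. Weighted: 0.480 and 0.397. The standard error is 0.1548, z = 2.304, and power is Φ(0.344) = 63.5%.

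The loss is 7.1 points. The same formula gives 92.3% − 87.2% = 5.1 points for rate 2.5, k = 0.5, and 46.9% − 41.7% = 5.2 points for rate 1.0, k = 2. All three lie within 4 to 10.

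**4. Does the model itself cost power?** In the first simulation, linear regression on the 9-month data gave 57.0%, 88.8% and 41.5% in the order of the table, against 58.8%, 89.8% and 42.7% for NB. The difference is 1 to 2 points. The second simulation gave 63%, 85% and 41% against 63%, 87% and 41%.

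**5. Ignoring exposure.** Assumed: the same true rate of 1.5 per year in both arms, k = 1, 192 per arm, and raw 12-month counts compared without adjustment for time observed. Type I error was 5.0% with 20% loss in both arms, 6.6% at 20% against 30%, and 12.8% at 10% against 30%.

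**The case against.** Several stronger readings are tempting, and the article does not support them.

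- **A promised 12-month rate is a quarter unobserved.** No section promises a cumulative 12-month rate. Read with the visit schedule, the outcome may be a 3-month rate at each visit, parallel to the questionnaires. The gap then limits what is estimated and contradicts nothing. This stands, but the article does not say which rate is meant, and windows cut short by death or transplant remain on either reading.
- **Months 7-9 are never observed.** This is certain for self-report only. Records are extracted as well and no date range is stated. That they cover only the recalled windows is the natural reading of their verifying role, not an explicit statement.
- **The named models cannot analyze the outcome.** Step 4 shows that a linear model on counts loses almost nothing.
- **Dichotomizing would cost far more.** It would, but nowhere does the article say that encounters will be reduced to any or none, so that loss cannot be charged to it.
- **A count model may be in the analysis plan.** That is fair: its absence from a condensed article would not be a finding alone. The collection windows are different, because a later plan cannot restore uncollected events.
- **Events before death are dropped.** Only those after the last completed visit are at risk. Missing Data keeps participants with at least one follow-up measure, so earlier reports stay in. Nothing in the article suggests that loss will differ by arm.

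**Conclusion.** The point holds as a weakness in how a primary outcome is collected and defined. As written, 3 of 12 months lie outside every recall window, events between the last visit and death or transplant are not captured, and no model is matched to a rate with unequal observation time. Under assumed control rates of 1.0 to 2.5 per year, dispersion 0.5 to 2 and a rate ratio of 0.70, the months 7-9 gap costs about 4 to 10 points of power. Those inputs are not in the documents, and clustering is ignored. With equal loss in the two arms, ignoring exposure leaves type I error near 5%; harm appears mainly when loss differs. This should be changed, but it does not undermine the trial or the HLQ power statement.

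**What to change.** - **Collection.** In both arms, extract unscheduled admissions, emergency visits and unscheduled dialysis from the electronic records continuously, from randomization to 12 months, death, transplant or withdrawal, whichever comes first.
- **Endpoint.** State that the primary endpoint is the event rate over that observed time. Keep the 3-month self-report at each visit as supplementary.
- **Analysis.** Use negative binomial regression with a log person-time offset, study arm, patient type and the planned center random effect. A count for the 3 months before randomization is an optional covariate if approvals allow; its absence is not an error.

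**Cost.** No visit is added. A record extraction already planned gets a wider date range, and the article does not state whether existing approvals cover that. Encounters outside the participating services may still be seen only in self-report, which is a reason to keep it.
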